### Primary outcomes

Number of participants with POCD at 3 months after surgery.Number of participants with POCD at the time of discharge from the acute clinic.Number of participants with POD during the stay in the intensive care unit.Number of participants with POD during the stay in the normal ward.

### Secondary outcomes

Change from baseline cognitive failures in everyday life (CFQ) at 3 months after surgery.Change from baseline health-related quality of life (SF-36) at 3 months after surgery.Changes from baseline neuropsychological parameters at the end of cognitive training.Number of participants with POCI at 3 months after surgery.Number of participants with POCI at the time of discharge from the acute clinic.

### Planned statistical analyses

Postoperative cognitive decline is defined as a decline and POCI as an improvement from pre- to post-assessment of at least 1 SD in at least 20% of all neuropsychological subdomains (4). The difference of 1 SD between pre- and post-assessment will be measured using Z-scores, defined by the difference in individual raw values from the mean value of the total baseline data divided by the SD of the total baseline data. We will use the criteria of the *Diagnostic and Statistical Manual of Mental Disorders* (DSM-5) (19) to define neuropsychological subdomains, as shown in Table 2. As some neuropsychological parameters can be contextually grouped into cognitive subdomains (see Table 2), we will summarize them by the mean value. POCD/POCI at the time of discharge from the acute clinic is defined as a decrease or increase between pre-examination and post-examination of 1 SD within the total score of the MOCA screening test. POD is defined as the occurrence of at least one delirious episode during the stay in the intensive care unit or normal ward. POCD/POCI and POD will be compared with Pearson's chi-square test (or Fischer's exact test). The effect size will be reported by odds ratio (OR) with a 95% confidence interval (CI).

**Table 2 T2:** Definition of neuropsychological parameters and cognitive subdomains.

**Cognitive domain (DSM-5)**	**Cognitive subdomains (DSM-5)**	**Neuropsychological parameter**	**Task (scale of measurement)**
Learning and memory	Visual immediate memory span	BVMT-R	Recalling objects immediately (number of correct items)
	Visual free recall	BVMT-R	Recalling objects after delay (number of correct items)
	Visual recognition memory	BVMT-R	Recognizing between learned and new objects (number of correct items)
	Verbal immediate memory span	VLMT	Recalling items of word list (number of correct items, first trial)
	Verbal free recall	VLMT	Recalling items of word list (summarized number of correct items, learning trials)
		VLMT	Recalling items of word list (number of correct items, short delay)
		VLMT	Recalling items of word list (number of correct items, long delay)
	Verbal recognition memory	VLMT	Recognizing between learned and new words (number of correct items)
Complex attention	Selective attention	TMT-A (speed)	Linking numbers in ascending order (seconds)
Executive functions	Verbal working memory	LNS	Mentally reorganization of letters and numbers (span)
	Cognitive flexibility	TMT-B (speed)	Linking numbers and letters in alternately order (seconds)
	Inhibition	SKT-7	Naming interfering letter, e.g., “S” instead of “T” (seconds)
Language	Word fluency	RWT (phonetic)	Naming words with specific initial letter (number of correct items)
		RWT (semantic)	Naming words from a specific category (number of correct items)
Perceptual motor	Visuo-construction	MOCA (3-D figure)	Drawing a 3-D figure (number of correct items)

BVMT-R, Brief Visuospatial Memory Test-Revised; VLMT, Verbaler Lern- und Merkfähigkeitstest (Auditory Verbal Learning and Memory Test); TMT, Trail Making Test; LNS, Letter Number Span; SKT, Syndrom-Kurztest Test (Short Performance Test); RWT, Regensburger Wortflüssigkeits-Test (Regensburger Word Fluency Test); MOCA, Montreal Cognitive Assessment.

Analyses of covariance (ANCOVAs) will be conducted to determine the effects of cognitive training on each neuropsychological parameter, CFQ, SF-36, and HADS-D. In the ANCOVA, the postoperative test value will be the dependent variable, groups will be the fixed factor, and the preoperative test value will be the covariate. Confounder variables that could affect the results will be implemented in addition to the preoperative cognitive values as further covariates to the ANCOVA. Confounder variables are defined as whether a correlation analysis among demographic variables, perioperative details, and neuropsychometrical changes between pre- and postoperative testing is significant.

Assumptions for ANCOVAs will be tested using a visual inspection of QQ and distribution plots of the dependent variable for normality, the Levene test for variance-homogeneity of the dependent variable, and a statistically significant correlation between the dependent variable and covariate (preoperative test value) calculated with Pearson's product–moment correlation. When assumptions for the ANCOVA are violated, difference values between pre- and post-tests will be calculated, followed by Mann–Whitney U-tests for between-subject effects. The effect sizes of continuous results will be given in η2.

If peri- and postoperative complications such as delirium, stroke, cardiovascular events, or other complications occur which could affect neuropsychological performance, and if these factors are unbalanced between the groups, we will calculate a subgroup analysis without those patients to reveal a more stringent outcome effect. In addition, we will perform subgroup analyses for each of the individual surgery cohorts, including AVR, MVR, CABG, and combination surgeries (AVR+MVR, CABG+AVR, CABG+MVR, and CABG+AVR+MVR) if the sample size of these subgroups allows for statistical analysis. Perioperative medical conditions or drug factors may have an impact on cognitive function. With the randomization principle, we expect these to be equally distributed between the groups. Otherwise, if the groups differ with respect to these factors, these can be accounted for in a subgroup analysis.

All analyses will be performed using the statistical software SPSS (version 22) and JASP (version 0.12.2).

Furthermore, interim analyses will be carried out during the investigation period to identify adverse events, overwhelming effects, or futility of the intervention arm. In this case, the study could be terminated before its planned completion. The decision will be made by the members of the study team.

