### Randomization

Randomization will be implemented using a computer-generated randomization list (www.randomization.com) with a 1:1 blocked allocation ratio and block sizes of 10. The randomization list will be generated, sequentially numbered, and concealed before the start of the study by the randomization list holder, who is located in the department of Neurology at the University Hospital Giessen and Marburg. After recruitment and the first preoperative neuropsychological examination, a study coordinator will allocate patients to the cognitive training or control group. A study coordinator will inform the psychological training supervisor about which patients should be trained.

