Baseline demographics and characteristics will include age, gender, years of educational and occupational background, body mass index, preexisting medical conditions (arterial hypertension, diabetes mellitus, dyslipidemia, and severity partition for left ventricular ejection fraction [defined by Lang et al. (18)]), heart failure, renal insufficiency (defined by a creatinine value above the in-house norms (men: >1.2 mg/dl, women: >0.9 mg/dl)), preoperative medication, type of surgery (CABG, AVR, MVR, and combination surgery), anesthesia and analgesics administered (type, amount, and duration), duration of the operation, duration of extracorporeal circulation, cross-clamp time, lowest body temperature, invasive ventilation time, peri- and postoperative complications (delirium, arrhythmia, atrial fibrillation, renal insufficiency, acute blood loss anemia, transient ischemic attack, stroke, dysarthria, aphasia, and death), days on the intensive care unit, and the total length of stay on the normal ward. We plan no systematic and standardized pre- or postoperative neuroradiological imaging.

The study process is shown in Figure 1. A detailed trial schedule according to the SPIRIT guidelines for study protocols is shown in Table 1 (17).

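### The ANCOVA covariates are chosen by a significance screen that can admit variables arising after randomisation, so the 3-month comparisons can lose part of the training effect

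*Protocol article*

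**What the plan says.** All references are to the protocol article.

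- **Base model** (Planned statistical analyses): "the postoperative test value will be the dependent variable, groups will be the fixed factor, and the preoperative test value will be the covariate". It is applied to each neuropsychological parameter, CFQ, SF-36 and HADS-D.
- **Extra covariates** (same section): "Confounder variables that could affect the results will be implemented in addition to the preoperative cognitive values as further covariates to the ANCOVA".
- **How they are chosen** (same section): "Confounder variables are defined as whether a correlation analysis among demographic variables, perioperative details, and neuropsychometrical changes between pre- and postoperative testing is significant".
- **Timing** (Randomization): "After recruitment and the first preoperative neuropsychological examination, a study coordinator will allocate patients to the cognitive training or control group". Training, the second test at admission and surgery all follow.
- **What is recorded** (Study process): one list, introduced as baseline information, runs from age and education to "duration of the operation, duration of extracorporeal circulation, cross-clamp time, lowest body temperature, invasive ventilation time", then to "peri- and postoperative complications (delirium, arrhythmia, atrial fibrillation, renal insufficiency, acute blood loss anemia, transient ischemic attack, stroke, dysarthria, aphasia, and death", then to days in intensive care and on the ward.
- **Delirium as an outcome** (Primary outcomes): "Number of participants with POD during the stay in the intensive care unit", with a matching count for the normal ward.
- **Complications** (Planned statistical analyses): if delirium, stroke or other complications are unbalanced between arms, a further analysis leaves those patients out.

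**The concern.** Two things are wrong with the rule as written.

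First, correlation with the outcome change does not show that a variable is a confounder. Randomisation already deals with confounding of the arm comparison by baseline variables. What the screen finds is prognostic variables, mediators and chance correlations.

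Second, perioperative details are in the pool by name, and nothing confines the pool to what was known at randomisation. Ventilation time, days in intensive care and, on one reading, delirium arise later. The trial's premise is that training protects against delirium and cognitive decline, so at least some of these may lie on the path from training to the 3-month score. The more strongly such a variable is tied to cognitive decline, the more surely it passes the screen.

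At stake is what the 3-month analyses estimate. With a mediator in the model, the arm coefficient is no longer the whole effect of training. CFQ and SF-36 at 3 months are listed secondary outcomes, and the Discussion makes better quality of life part of the case for adopting the programme.

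**Working it through.** **1. The plan's own figure.** Inputs from Power and sample size estimation: d = 0.65, alpha 0.05, power 0.8, ANCOVA. For two equal groups f = d/2 = 0.325. The noncentrality is f² × N = 0.105625 × 77 = 8.13, with 1 and 77 − 2 − 1 = 74 degrees of freedom. Power is 0.7984 at N = 76 and 0.8036 at N = 77, so 77 is reproduced. For dropout, 77 / (1 − 0.23) = 100.

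**2. Which analyses are exposed.**

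| Analysis | Measured | Exposed to adjustment for a mediator? |
|---|---|---|
| POD, POCD (primary), POCI | in hospital, 3 months | No: unadjusted chi-square or Fisher test |
| Test parameters at end of training (the powered outcome) | at admission, usually the day before surgery | No: surgery has not yet happened |
| CFQ, SF-36 (secondary) | 3 months | Yes |
| Test parameters, HADS-D | 3 months | Yes |

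**3. What adjustment does.** Let training act on the 3-month score directly (c) and by lowering the POD rate from p_C to p_T, where POD costs b:

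total effect = c + b × (p_C − p_T)

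With POD in the model, the arm coefficient estimates c alone.

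The document gives neither b nor c, so these are assumptions. The POD rates lie within the 14 to 50% cited in the Introduction. With p_C = 0.50, p_T = 0.25, b = 0.8 SD and c = 0.3 SD:

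total = 0.3 + 0.8 × 0.25 = 0.50 SD; adjusted = 0.30 SD

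**4. Simulation of the rule.** N = 77 (taken as evaluable at 3 months), 3,000 runs per scenario, pre-post correlation 0.6. The score is 0.6 × pre + c × arm − b × POD + noise. POD enters the ANCOVA, beside the pre score, when its correlation with the pre-to-post change has p < 0.05. Eight of the 13 scenarios run:

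| POD control / training | b | c | True total | Estimate, pre score only | Estimate, rule | POD selected | Power, pre score only | Power, rule |
|---|---|---|---|---|---|---|---|---|
| 50 / 14% | 0.8 | 0 | 0.288 | 0.285 | 0.005 | 95% | 0.294 | 0.055 |
| 50 / 14% | 0.8 | 0.3 | 0.588 | 0.588 | 0.298 | 98% | 0.829 | 0.304 |
| 50 / 14% | 1.2 | 0.3 | 0.732 | 0.734 | 0.300 | 100% | 0.908 | 0.311 |
| 50 / 25% | 0.8 | 0 | 0.200 | 0.199 | 0.004 | 96% | 0.163 | 0.052 |
| 50 / 25% | 0.8 | 0.3 | 0.500 | 0.510 | 0.312 | 98% | 0.702 | 0.373 |
| 30 / 15% | 0.8 | 0 | 0.120 | 0.120 | 0.008 | 88% | 0.100 | 0.048 |
| 30 / 15% | 0.8 | 0.3 | 0.420 | 0.420 | 0.301 | 93% | 0.560 | 0.353 |
| 30 / 30% (null) | 0.8 | 0 | 0 | −0.001 | 0.002 | 94% | 0.047 | 0.044 |

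In the 12 scenarios with an effect, POD was selected in 88 to 100% of runs and the estimate fell to about c. In the null row, rejection stays near 5%.

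**5. Chance selections.** With 25 irrelevant candidates, 25 × 0.05 = 1.25 enter on average. A separate simulation of 4,000 trials at N = 77 gave type I error 0.0525 with 25 candidates and 0.052 with 40. The harm comes from mediators, not from noise variables.

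**6. Cost of a fixed set.** With five covariates in place of one, the error degrees of freedom fall from 74 to 77 − 2 − 5 = 70, and power at N = 77 goes from 0.8036 to 0.8031.

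**The case against.** The strongest objection is that the selection rule never names delirium. The list under Study process says what is recorded; it does not define a covariate pool. Complications have their own treatment, the analysis without affected patients. Perioperative details may then mean only operative ones, such as bypass and cross-clamp times, which home paper-and-pencil training is unlikely to change. Adjusting for those would not remove its effect.

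Part of this stands. Delirium's place in the pool is an inference, and the worked example depends on it. But nothing excludes it, the only list of such variables files it under baseline information, and the separate analysis does not take complications out of the pool. That analysis itself conditions on events after randomisation. Ventilation time and intensive-care days raise the same question without delirium.

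Three stronger readings are tempting and are not supported:

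- **That adjustment reverses the sign.** A reader might infer this from regressing the score on arm and delirium alone. With a latent vulnerability assumed to drive both delirium and outcome, and no direct effect, that gives about −0.06 SD (POD 30 vs 15%) or −0.10 SD (50 vs 25%). But the planned ANCOVA always contains the preoperative score. If that score correlates 0.6, 0.8 or 1.0 with the vulnerability, the figures shrink to −0.04, −0.02, 0.00 and −0.07, −0.04, 0.00. Without shared vulnerability the adjusted estimate is 0.00. Reversal needs a vulnerability that the baseline score misses and little or no direct effect, and the document gives no figure for either.
- **That each test parameter gets its own covariate set.** This may happen, but the text does not say whether the screen runs once or per parameter.
- **That the main conclusions are at risk.** The primary comparisons are unadjusted and the powered outcome precedes surgery.

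**Conclusion.** The point holds for the postoperative ANCOVAs of the neuropsychological parameters, CFQ, SF-36 and HADS-D. The article states a selection rule, so this is not a detail left to a later plan, and the rule can admit variables that training may change. Any part of the effect that runs through an admitted variable is then lost from the estimate.

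The document does not fix the size. In the example with a direct effect of 0.3 SD and POD at 50 vs 25%, the estimate falls by 0.51 − 0.31 = 0.20 SD and power from 0.70 to 0.37. With no direct effect, the estimate falls to about zero. These figures assume that delirium is admitted, that it costs 0.8 SD, that training lowers its rate, that the pre-post correlation is 0.6 and that 77 patients are evaluable at 3 months. If training changes none of the admitted variables, this loss does not arise. The consequence is a wrong estimand and lost power, not false positives.

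**What to change.** In Planned statistical analyses, replace the significance screen with one short, prespecified covariate set measured before randomisation and used in all main ANCOVAs: the t0 score plus, for example, age, years of education and planned type of surgery. Name t0 explicitly, because Table 1 has two preoperative assessments and the one at admission comes after training.

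State that variables arising after randomisation (operative details, ventilation time, complications including delirium, intensive-care and ward days) stay out of the main arm comparisons. Analyses adjusted for them can remain if labelled exploratory. Under Study process, separate the true baseline variables from those recorded during and after surgery.

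The cost is a few sentences and a few degrees of freedom. N = 77 (100 with dropout) is unaffected. The change should be made before outcome data are seen by arm.

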### Power and sample size estimation

Because there are currently no effect sizes for extensive paper-and-pencil-based preoperative cognitive training in cardiac surgical patients using extracorporeal circulation, and because their influence on the incidence of POD and POCD is unclear, we have estimated sample size based on the effect sizes of general cognitive training in older healthy individuals, which ranges between d = 0.4 and d = 0.9 (20, 21). To not underestimate or overestimate the required sample size, we use an average value of d = 0.65. To find an effect size of d = 0.65 at a test power of 0.8 (alpha = 0.05) within an ANCOVA, a sample size of 77 subjects is required. With an estimated dropout rate of 23% in the preoperative test phase, the total sample size will be 100 subjects. The sample size per group is thus 50 patients. We used the analysis software G^*^Power-3 to calculate the sample sizes and the statistical power (22). We want to note that the power analysis refers to our secondary outcome “Changes from baseline neuropsychological parameters at the end of cognitive training.” Accordingly, the primary outcomes regarding the incidence of POD and POCD will be calculated exploratively.

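### A significant outcome–baseline correlation is wrongly made a condition for ANCOVA, and the fallback (unadjusted Mann–Whitney on change scores) is least efficient when that condition fails

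*Protocol article*

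**What the plan says.** All of this is in the protocol article. Under Planned statistical analyses, each neuropsychological parameter, the CFQ, the SF-36 and the HADS-D are analysed by ANCOVA, in which "the postoperative test value will be the dependent variable, groups will be the fixed factor, and the preoperative test value will be the covariate". Confounders that correlate with the outcome changes are to be added as further covariates.

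Three checks decide whether that model is used:

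- "visual inspection of QQ and distribution plots of the dependent variable for normality"
- "the Levene test for variance-homogeneity of the dependent variable"
- "a statistically significant correlation between the dependent variable and covariate (preoperative test value"), by Pearson correlation

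The consequence of a failure follows: "When assumptions for the ANCOVA are violated, difference values between pre- and post-tests will be calculated", and these go to Mann–Whitney "U-tests for between-subject effects". No other fallback is given.

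Power and sample size estimation sizes the trial on this analysis. It says "we use an average value of d = 0.65" and that, "at a test power of 0.8 (alpha = 0.05) within an ANCOVA, a sample size of 77 subjects is required". The section states that this calculation refers to the secondary outcome of change in neuropsychological parameters at the end of training.

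**The concern.** In a randomised comparison ANCOVA is valid whether or not the covariate predicts the outcome. A useless covariate costs about one degree of freedom and causes no bias; the analysis then nearly equals a comparison of post values. Lack of correlation is therefore no reason to leave the model.

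The remedy also points the wrong way. Subtracting a baseline that hardly predicts the outcome adds the baseline's noise to the outcome. The third check fails only when the correlation is low, which is where a change score performs worst. The fallback also discards the baseline covariate and any confounders that the plan meant to adjust for.

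Separately, the normality and variance conditions of ANCOVA concern the residuals. The raw outcome also carries spread due to baseline and group, so its shape is the wrong trigger.

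At stake is the power of the only outcome family with a sample-size justification. In addition, different parameters may be tested by different methods chosen after the data are seen.

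**Working it through.** **1. The plan's own figure.** Inputs from Power and sample size estimation: d = 0.65, power 0.80, alpha 0.05 (taken as two-sided, as for an F test). With f = d/2 = 0.325 and N = 77, the noncentrality is λ = N·f² = 77 × 0.1056 = 8.13. With 1 and 77 − 2 − 1 = 74 degrees of freedom, power is 0.804; N = 76 gives 0.798. So 77 is reproduced, and 77/(1 − 0.23) = 100.

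**2. When the correlation condition fails.** The critical value at N = 77 is r = t/√(75 + t²) with t = 1.992, which gives 1.992/√78.97 = 0.224. Any sample |r| below that diverts the parameter.

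**3. Efficiency.** Take equal pre and post SDs of 1 and true correlation r. The variance of post − b·pre is 1 + b² − 2br.

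- Post value only (b = 0): 1
- Change score (b = 1): 2(1 − r)
- ANCOVA (b = r): 1 − r²

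The change score exceeds ANCOVA by 2(1 − r) − (1 − r²) = (1 − r)², so it never does better. It beats the post value alone only if r > 0.5. At r = 0.224 the variances are 1.55 (change), 1.00 (post only) and 0.95 (ANCOVA), and the change/ANCOVA ratio is 1.63. At r = 0 it is 2.00.

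**4. Power once diverted.** λ is 8.13/(1 − r²) for ANCOVA and 8.13 × 0.955/[2(1 − r)] for Mann–Whitney on change, where 0.955 is its efficiency under normality. d is taken in units of the post-score SD.

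| r (assumed) | λ ANCOVA | Power | λ Mann–Whitney on change | Power |
|---|---|---|---|---|
| 0 | 8.13 | 80% | 3.88 | 49% |
| 0.2 | 8.47 | 82% | 4.85 | 59% |
| 0.5 | 10.84 | 90% | 7.77 | 79% |
| 0.7 | 15.95 | 98% | 12.94 | 94% |

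The first two rows are where the correlation condition tends to fail. The last two matter only if normality or the Levene test triggers the switch.

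**5. Power of the rule as written.** Step 4 ignores how often the switch happens. The correlation condition plus fallback was therefore simulated with bivariate normal data, N = 77 and d = 0.65. Repeat runs agree to about one percentage point.

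| True correlation (assumed) | Condition fails | ANCOVA kept | Rule as written |
|---|---|---|---|
| 0 | 95% | 80% | about 50% |
| 0.1 | 88% | 80% | about 57% |
| 0.2 | 61% | 81% | about 68% |
| 0.3 | 28% | 83% | about 80% |
| 0.4 | 7% | 86% | 86% |
| 0.5 | 0.6% | 90% | 90% |

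With no treatment effect, the rejection rate was about 5% for both approaches at every correlation.

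**The case against.** The strongest reply is that these are repeated administrations of the same tests, and such scores may well correlate at 0.5 or more. The correlation condition then fails in under 1% of trials and the rule is harmless. This stands as a limit on size. The article gives no r, so the low-correlation rows are assumptions, and no parameter can be shown from the document to be that weak. It does not rescue the rule, which does nothing useful at high r and harm at low r.

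A reader might infer that every diverted parameter loses much of the stated 80%. The figures do not support that. A switch triggered by shape at r of 0.5 to 0.7 gives up efficiency relative to ANCOVA (90 to 79%, 98 to 94%) but leaves power near or above 80%. Those figures are normal-theory ones and do not describe skewed data. In one assumed lognormal model (log-SD 0.4, d = 0.65 on the log scale), Mann–Whitney on raw change had 71% power at r = 0.5 and 89% at 0.7, against about 86% and 96% for ANCOVA on raw values. The direction is the same, but the size depends on the model.

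A reader might also infer that the three tests scored in seconds are diverted needlessly because raw values are inspected. That does not follow: if such times are skewed, their residuals may be skewed too. The error is that the wrong quantity is inspected, whatever the result.

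Finally, robust standard errors or compulsory log transformation are reasonable preferences that an analysis plan may settle. Their absence from the article is not a fault.

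**Conclusion.** The point holds in limited form. The correlation condition is a statistical error in the stated rule, and nothing else in the article corrects it. Where the condition fails, the fallback is the least efficient of the usual options.

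The cost is up to about 30 percentage points of power at zero correlation (80 to 50%), about 13 at 0.2, about 3 at 0.3, and negligible from 0.4. This rests on an assumed range for r, bivariate normality, equal pre and post SDs, N = 77, and d = 0.65 in post-score SD units. The article does not say which SD it means. If d refers to the residual SD, ANCOVA power is 80% at every r and the fallback's power is lower than shown, but the variance ratio is unchanged.

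The harm is confined to weakly correlated continuous secondary parameters, which belong to the family the trial is powered on. Two larger readings are not supported. The correlation condition does not inflate false positives in the simulation. It also does not touch the delirium and cognitive-decline incidences, which are compared by chi-square or Fisher's test. Checking raw scores instead of residuals is a second, smaller fault.

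**What to change.** In Planned statistical analyses:

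1. Delete the requirement of a significant correlation between outcome and preoperative value.
2. Keep the baseline-adjusted ANCOVA for every continuous parameter.
3. Judge normality and variance homogeneity on the model residuals.
4. Where residuals are poor, replace Mann–Whitney on change scores with a fallback that keeps baseline adjustment. Examples are ANCOVA on a pre-specified transformation (such as log seconds for TMT-A, TMT-B and SKT-7) or rank ANCOVA.

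The cost is a few sentences and minor extra analysis work. Design, data collection and sample size do not change.

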In addition to altering preoperative cognitive performance to potentially counteract POD and POCD, other risk factors regarding POD such as poor sleep burden (50) and heart rate response/recovery to exercise (51) can also be modified in the preoperative setting and may be linked to preoperative risk factors such as depression and reduced cognitive functions.

Should it become evident that the use of our cognitive training can both reduce the incidence of POCD and POD and improve health-related quality of life, one possibility could be to integrate this intervention into a standardized prehabilitation program. It can also be evaluated in other patient populations affected by postoperative neurocognitive dysfunctions.

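### For continuous outcomes the protocol names only η², without a confidence interval, so it does not commit to reporting the size, direction or precision of the training effect

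*Protocol article*

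**What the plan says.** Under Planned statistical analyses, ANCOVAs are to be run "to determine the effects of cognitive training on each neuropsychological parameter, CFQ, SF-36, and HADS-D". In the model, "the postoperative test value will be the dependent variable, groups will be the fixed factor, and the preoperative test value will be the covariate". If the ANCOVA assumptions fail, "difference values between pre- and post-tests will be calculated, followed by Mann–Whitney U-tests for between-subject effects". The effect measure for all of this is one sentence: "The effect sizes of continuous results will be given in η2". It gives no interval and does not say whether η² or partial η² is meant.

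The same section treats the binary outcomes (POCD, POCI, POD) differently: "The effect size will be reported by odds ratio (OR) with a 95% confidence interval (CI").

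Under Power and sample size estimation the trial is sized on a standardised mean difference ("we use an average value of d = 0.65"). The authors note there that this calculation refers to the secondary outcome of neuropsychological change at the end of training. The outcome that drives the sample size is therefore among those to be summarised by η².

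**The concern.** The continuous secondary outcomes are defined as changes from baseline, so the natural questions are how much, which way and how surely. η² alone answers none of them.

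- **Direction.** η² cannot be negative, so a benefit and a harm of equal size give the same value. The scales also run in opposite directions. Table 2 lists TMT-A, TMT-B and SKT-7 in seconds, where more is worse. The CFQ records how often failures occur, so more is worse if it is scored upward from never. On the SF-36 a higher score is better. A table of η² values would not show which rows favour training.
- **Unit.** η² is not expressed in words recalled, seconds or SF-36 points.
- **Precision.** No interval is planned. In a sample of about 77, an interval is what shows whether a useful gain or a harm has been excluded.
- **Meaning.** The same label is to cover an ANCOVA with baseline only, an ANCOVA with further covariates, and a Mann-Whitney test. With covariates, η² and partial η² differ, and the protocol does not say which is intended.

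The Discussion makes wider use of the programme depend on evidence that it "can both reduce the incidence of POCD and POD and improve health-related quality of life". The quality-of-life half of that condition needs a signed effect with an interval.

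**Working it through.** **Inputs.** d = 0.65 (range 0.4 to 0.9), power 0.80, alpha 0.05, 77 analysable, 23% dropout and 100 in total, all from Power and sample size estimation; 1:1 allocation, from Randomization. Assumption: 77 patients split 38 and 39.

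**1. The plan's own figure.** For two groups, f = d/2 = 0.325. The noncentrality at N = 77 is λ = N·f² = 77 × 0.1056 = 8.13. With 1 and 74 degrees of freedom (one covariate), power is 0.804, and 77 is the smallest N that reaches 0.80. Then 77/(1 − 0.23) = 100. The stated 77 and 100 reproduce.

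**2. The planning effect on the η² scale.** η² = d²/(d² + 4).

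| d | η² |
|---|---|
| ±0.40 | 0.16/4.16 = 0.038 |
| ±0.65 | 0.4225/4.4225 = 0.096 |
| ±0.90 | 0.81/4.81 = 0.168 |

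The sign of d is lost in every row. With no true effect, the expected η² is about 1/76 = 0.013, not zero.

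**3. Precision behind a single value.** Ignoring the covariate, SE(d) ≈ √(1/38 + 1/39) = 0.228. With t(0.975; 74 df) = 1.99, an observed d of 0.65 has a 95% CI of 0.65 ± 0.454, or 0.20 to 1.10. The corresponding F is (0.65/0.228)² = 8.13, so partial η² = 8.13/(8.13 + 74) = 0.099. Inverting the noncentral F gives a 95% CI of about 0.01 to 0.23 on that scale.

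**4. What the planned model gives.** An ANCOVA was fitted to one constructed data set of 77 (baseline covariate, group effect set to +0.65 and then to −0.65).

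| True effect | Partial η² | Adjusted difference (95% CI) |
|---|---|---|
| +0.65 | 0.116 | +0.65 (0.23 to 1.07) |
| −0.65 | 0.116 | −0.65 (−1.07 to −0.23) |

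The η² column cannot tell the two rows apart; the adjusted difference can, and it comes from the same fit. The values differ slightly from step 3 because they come from a single generated sample. They illustrate the point and do not predict the trial's interval.

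**The case against.** A reader might infer that every continuous result will appear only as η², and that the trial therefore cannot say how much cognition or quality of life changed, or in which direction. The document does not support that. The sentence fixes the effect-size index and does not exclude means, adjusted means or differences. The ANCOVA yields a signed, baseline-adjusted difference, and the fallback works on signed change scores. Decline and improvement are counted separately at discharge and at 3 months, each with an OR and CI. The Dissemination policy promises publication whatever the size or direction of the effect. All of this stands.

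It can also be said that choosing η² for an ANCOVA is conventional, that it converts to and from d for equal arms, and that an article leaves detailed output to a fuller document. The conversion argument is partly right. Given its degrees of freedom, a partial η² can be turned back into F (0.099/0.901 × 74 = 8.13), and from there into an unsigned d with an interval. The sign and the scale units cannot be recovered in this way.

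The appeal to a fuller document carries less weight. The article does specify effect reporting at this level: it names a measure with an interval for binary outcomes and a different measure, without one, for continuous outcomes. That is a stated choice and can be judged as such. The POCD and POCI counts do not cover the end-of-training assessment, the CFQ or the SF-36. The dissemination pledge names no estimator.

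**Conclusion.** The point holds as a weakness in the stated reporting plan. The only effect measure named for the continuous outcomes, including the powered one, has no direction or unit and is planned without an interval. At the planning effect, benefit and harm both map to 0.096. A result exactly at that effect would be compatible with roughly 0.20 to 1.10 SD, which the single value does not show. This interval rests on 77 analysed patients in near-equal arms and ignores the covariate, so the ANCOVA interval may be narrower.

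The consequence is limited. The data and the model allow the right estimate, no test or sample size is wrong, and the affected outcomes are secondary. The change is still worth making: it costs almost nothing, it concerns the outcome the trial was sized for, and naming the estimate in advance removes a later choice of metric.

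**What to change.** Replace the η² sentence in Planned statistical analyses with wording such as:

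> For each continuous outcome, the baseline-adjusted mean difference (training minus control) from the ANCOVA will be reported in the units of the scale with its 95% CI, optionally also as a standardised d. Where the Mann-Whitney test is used, the Hodges-Lehmann shift in change scores (training minus control) will be reported with its 95% CI. Partial η² may be added as a supplement.

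Tables should state for each scale which sign favours training.

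The cost is one sentence of protocol text. The adjusted difference and its interval come from the model already planned, and the shift estimate uses the change scores already planned for the fallback. No further data are needed, and sample size, tests and alpha stay as they are.
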